#### 4. METHODS:

**Methods to evaluate the Alternative Response Unit (AR2):**

**Quasi-experimental studies showing relationship between urban blight remediation and overdoses.**

We will evaluate the impact of blight remediation on fatal and nonfatal opioid overdoses using quasi-experimental methods. Across the AR2 dispatch zone, various vacant lots that have been cleaned and greened will serve as our treatment group. Randomly selected control lots will be matched to these treated lots. We will perform regression analyses to understand associations between blight remediation and overdoses.

**Methods to evaluate the impact of blight remediation on fatal and nonfatal opioid overdoses:**

**Using 360° photographs to measure level of blight in the neighborhood environment.**

360° photographs will be taken of the immediate surrounding outdoor environment where AR2 responses occur and where the control participants were at that same time. Photographs will be coded and analyzed. We will use this photographic technique to evaluate the level of blight around AR2 engagements.

**4.1. Study Instruments:** We will develop an interview guide for interviews which will include, when relevant: the perception of the AR2, their experience taking care of overdose patients, and challenges they face while working as part of the AR2, and their suggestions for improvement.

**4.2. Group Modifications:** There will be no group modifications.

**4.3. Method for Assigning Subjects to Groups:** N/A

**4.4. Administration of Surveys and/or Process:**

**Process for Review of Databases:** We will use data from four different City of Philadelphia departments: Philadelphia Department of Public Health (PDPH), Philadelphia Fire Department (PFD), Department of Behavioral Health and Intellectual disAbilities, and Managing Director's Office (MDO). These data are not currently linked between departments (we have letters of support from each agency). AR2: the AR2 dispatch and encounter data will be shared from both the PDPH and PFD databases. These data include 1) date, time, and location for all AR2 interactions, 2) demographic information about each participant including name and date of birth, and home address (when available), and 3) information about which components of the AR2 intervention were delivered during each engagement and in follow up.

Data related to linkage to care outcomes will be extracted from the DBHIDS Enterprise Data Warehouse. This data system includes all Medicaid plus uninsured claims for substance abuse treatment and care in Philadelphia. There is robust Medicaid penetration among opioid users in Philadelphia. In 2017, there were over 15,000 unique beneficiaries with opioid use disorder using behavioral health services, up from 9,000 in 2010. DBHIDS has committed to sharing these data in a manner that can be linked to EMS and

AR2 visit. This ensures that we will be able to track the substantial number of people who use opioids and who remain in Philadelphia through the behavioral health system after they have come into contact with the AR2 or EMS.

Data regarding fatal opioid overdose will come from the PDPH through the Philadelphia Office of the Medical Examiner, which sits within the PDPH. These data will include the name, date of birth, and death location for all fatal opioid overdose victims. The second distal outcome is non-fatal overdose, data which will come from both the PFD and the PDPH. The PFD will provide data for all EMS overdose related encounters, including date, time, and location of the dispatch; patient name and date of birth; patient home address (when available); and outcome of encounter (refused transport vs. transport to a hospital).

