**Inclusion criteria for the comparator group include all EMS encounters where:**

- The encounter is for a presumed overdose
- Patients are at least 18 years of age
- Located within the Kensington area (AR2 dispatch zone) and areas that are immediately adjacent
- From May 1, 2019 to April 30, 2021 (24 months)

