- b. **Paired encounter analysis.** For the analysis of paired encounters (one AR2 and a non-AR2 occurring while the AR2 was on another call), we will use an exact McNemar's test for paired data for 0/1 outcomes (death, relapse) and a Cox proportional hazards model for paired data for censored time to event outcomes (time to treatment linkage, time to subsequent overdose). For each AR2 encounter we try to identify a non-AR2 encounter at the same time period within the AR2 response zone. If we find one, these pair of encounters are labeled as a pair and we will follow the patients for 60 days for linkage and non-fatal overdose, and 24 months for fatal overdose, and record outcomes. If multiple non-AR2 encounters happen simultaneously, then conditional logistic regression and stratified Cox models will extend the analysis from a 1-to-1 pairing to a 1-to-many matching. For our power calculations we assume a 1-to-1 pairing, a one-sided test for a reduction in adverse outcomes with  $\alpha = 0.05$  and a power level of at least 0.80. To detect a 50% reduction in the death rate attributable to the AR2 (assumed reduction from 10% to 5%), we need 370 pairs of encounters. To detect a 50% reduction in the rate of repeat non-fatal overdoses (from 30% to 15%), we need 105 pairs of encounters. To detect a 50% reduction in the hazard rate of time to subsequent overdose (equivalent to roughly 19% having a subsequent overdose within one year to 9.5%), we need 200 pairs of encounters. To detect an increase of 50% in the odds of seeking treatment within 60 days of an overdose (from 26% seeking drug treatment after an overdose within 60 days to 35% with AR2), we need 360 pairs of encounters.

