- c. **Comparisons across time discontinuities.** For outcomes underpowered with a paired analysis, we will compare AR2 encounters during AR2 operational hours (10AM-6PM) to non-AR2 encounters outside of AR2's operational hours (6PM-10AM) within the Kensington zip code. Since comparison encounters will not be occurring at the same times as the AR2 encounters, there is a risk of confounding. We will first assess whether AR2 and non-AR2 patients encountered differ on likely confounders (e.g. age, race, sex, substance use profile such as type of drug, injected or not). Ideally focusing exclusively on patient encounters closest to AR2 time boundaries (near 10AM and 6PM) will provide sufficient observations and minimize the risk of confounding. If we find no differences (e.g. patients overdosing earlier in the day resemble those who overdose later in the day) then we will analyze the data as a simple binomial test of proportions (for 0/1 outcomes) or estimate the hazard ratio (for time to event outcomes). If we do find differences, then we will propensity score reweight comparison cases on age, sex, race, and substance use profile so that they do match. The following power calculation assumes no propensity score reweighting, but if propensity score reweighting is needed, the effective sample size, computed as  $(\sum w_i)^2 / \sum w_i^2$  where  $w_i$  is the propensity score weight, will need to equal the needed sample size in the power analysis. This depends on how many comparison encounters closely resemble the AR2 patients. To detect a 50% reduction in the death rate

attributable to the AR2 (assumed reduction from 10% to 5%), we need 380 encounters in each arm. To detect a 50% reduction in the rate of repeat overdoses (from 30% to 15%), we need 105 encounters in each arm. To detect a 50% reduction in the hazard rate of time to subsequent overdose (equivalent to roughly 19% having a subsequent overdose within one year to 9.5%), we need 200 encounters in each arm. To detect an increase of 50% in the odds of seeking treatment within 60 days of an overdose we need 380 encounters in each arm.

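### Treatment linkage is visible only in Philadelphia Medicaid-plus-uninsured claims, and the day versus off-hours comparison does not check or adjust for who that file can see

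*Protocol*

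**What the plan says.** Section 4.4 names a single source for this outcome: "Data related to linkage to care outcomes will be extracted from the DBHIDS Enterprise Data Warehouse". It defines the content of that source as follows: "This data system includes all Medicaid plus uninsured claims for substance abuse treatment and care in Philadelphia". In support it says "There is robust Medicaid penetration among opioid users in Philadelphia" and cites more than 15,000 beneficiaries with opioid use disorder in 2017. It limits tracking to people "who remain in Philadelphia through the behavioral health system after they have come into contact with the AR2 or EMS".

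Sections 2.2 and 2.3 select patients by presumed overdose, age, place and date. For the comparator group, place means "Located within the Kensington area (AR2 dispatch zone) and areas that are immediately adjacent". No criterion concerns insurance or residence.

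Section 5.5, Aim 1, prefers paired encounters. Where pairs are too few, part (c) compares AR2 encounters in operating hours with non-AR2 encounters outside those hours. The example confounders to be checked are "age, race, sex, substance use profile such as type of drug, injected or not". If the groups differ, the plan is to "propensity score reweight comparison cases on age, sex, race, and substance use profile so that they do match"; if they do not, an unadjusted test or hazard ratio follows. Part (d) adds a difference-in-difference analysis using encounters outside zip code 19134. The Aim 1 comparator text in section 3.1 also allows a simple difference at a temporal or spatial boundary.

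The linkage sample sizes are 360 pairs ("from 26% seeking drug treatment after an overdose within 60 days to 35% with AR2"), 380 per arm for the time-of-day comparison, and 700 per area and time period for difference-in-difference.

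**The concern.** The endpoint is described as seeking treatment within 60 days, but what is recorded is publicly funded treatment in Philadelphia. A patient treated under private cover or Medicare, or in another county, cannot be observed to have the outcome. The protocol gives no separate rule for such patients, so following everyone for 60 days and recording what the file shows makes them non-events.

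This has two consequences. If visibility is equal in both groups, events are lost and the contrast shrinks. If it differs, an insurance or residence difference appears as a linkage difference when treatment does not differ, or hides a real one. Linkage is the proximal outcome of Aim 1. Its required number of pairs (360) is close to that for death (370), so use of the time-of-day fallback for linkage is a realistic prospect.

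**Working it through.** **Inputs from the protocol (section 5.5, Aim 1).** Linkage 26% without AR2; a 50% increase in odds, rounded there to 35%; one-sided alpha 0.05; power at least 0.80; 380 per arm. **Assumed, because the protocol does not give it:** the share v of patients whose treatment the file can see, taken between 70% and 100%.

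**1. Reproducing the plan's figure.** Odds of 26% times 1.5: (0.26/0.74) × 1.5 = 0.527, a rate of 34.5%. With n = [1.645√(2p̄q̄) + 0.842√(p₀q₀ + p₁q₁)]² / (p₁ − p₀)²:
- p̄ = 0.3026, so n = (1.0687 + 0.5444)² / 0.0851² = 359 per arm.
- With continuity correction, n = 383, which matches the stated 380 within rounding.
- Two-sided versions give 456 and 480 and do not match.

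The stated figure is therefore sound on its own terms, and those terms include that every linkage is observed.

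**2. Model for visibility.** Observed rate = v × true rate. Rejection probability = Φ{(|p₁ − p₀|√n − 1.645√(2p̄q̄)) / √(p₀q₀ + p₁q₁)}, with n = 380 per arm.

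**3. No AR2 effect (26% in both groups), visibility differing between groups.**

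| v, AR2 / comparison | Observed rates | Odds ratio | One-sided rejection (nominal 5%) |
|---|---|---|---|
| 0.90 / 0.88 | 23.4% / 22.9% | 1.03 | 7% |
| 0.90 / 0.80 | 23.4% / 20.8% | 1.16 | 22% |
| 0.90 / 0.70 | 23.4% / 18.2% | 1.37 | 55% |

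Second row in full: (0.026 × 19.49 − 1.645 × 0.5868) / 0.5865 = −0.78, and Φ(−0.78) = 0.22.

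The bias can also run the other way. With a true odds ratio of 1.5 and v = 0.85 for AR2 against 0.95 for comparison, the observed odds ratio is 1.27 and power is 42%.

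**4. Difference-in-difference, as a ratio of odds ratios.**
- No effect, the same time-of-day gap (0.95 v 0.85) in both areas: the gap cancels, ratio 1.00.
- True odds ratio 1.5, v constant over the day but 0.95 inside and 0.80 outside 19134: ratio 1.49.
- No effect, gap of 0.95 v 0.85 inside 19134 only, 0.80 at both times outside: false ratio 1.16.

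**5. Equal visibility, if 26% and 35% are all-payer rates.** Power at 380 per arm:

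| v | Observed rates | Power |
|---|---|---|
| 1.00 | 26.0% v 35.0% | 0.85 |
| 0.90 | 23.4% v 31.5% | 0.81 |
| 0.80 | 20.8% v 28.0% | 0.75 |
| 0.70 | 18.2% v 24.5% | 0.68 |

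**6. What adjustment can recover.** Take the 0.90 v 0.80 null case. Suppose a share r of visible patients has a prior record in the file, and linkage is 26% with or without one. Reweighting the comparison group to the AR2 group's record share (0.90r) gives a comparison rate of 0.26 × [0.90r + (1 − 0.90r) × 0.80(1 − r)/(1 − 0.80r)]. The false odds ratio of 1.16 falls only to 1.15 at r = 0.3 and 1.13 at r = 0.5. Restricting to patients known to be visible gives 26% v 26%, an odds ratio of 1.00 under the same model.

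**The case against.** The strongest reply is that the exposure is narrow and its size unknown. The preferred design pairs encounters at the same time in the same zone, where a payer difference is less likely. The time-of-day comparison is a fallback, and ideally it keeps to encounters near 10 AM and 6 PM, which should narrow any gap. The confounder check is introduced by examples, so payer could be added. No document shows that insurance differs by hour, and a two-point gap does little (odds ratio 1.03, rejection 7%). All of this stands and limits how firmly the point can be put. It does not close it: the reweighting list is closed, and the reassurance on Medicaid is a count of beneficiaries, not the visible share of this cohort or its constancy over the day.

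Two stronger readings are tempting and not supported.
- A reader might infer that every comparison using other zip codes is biased. In section 5.5, encounters outside 19134 enter only through difference-in-difference, which cancels a gap shared by both areas and nearly cancels a constant gap between areas. Only a time-of-day gap that differs between the areas remains. The simple spatial-boundary difference in section 3.1 is the exception.
- A reader might infer that 360 pairs or 380 per arm are too few. At 90% visibility, 380 per arm still gives 0.81 for 26% v 35%. The protocol also does not say whether the 26% comes from a payer-limited source; if it does, the loss is at least partly built in.

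Finally, counting unseen patients as not linked is an inference from the stated procedure. A separate analysis plan could set a different rule.

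**Conclusion.** The point holds in a limited form. The only named linkage source is restricted by payer and city, eligibility is not, and the plain day versus off-hours contrast and any simple spatial difference adjust for nothing that measures visibility. Neither the size nor the direction of bias can be fixed from the protocol. A gap of a few points between groups is minor. A gap of 10 points would roughly quadruple the one-sided error rate, from 5% to 22%. These figures assume equal true linkage among visible and unseen patients and 380 per arm with no reweighting. Power for linkage falls with visibility only if the planning rates are all-payer rates. This is worth correcting, at medium confidence, and does not undermine the paired analysis.

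**What to change.** For the linkage outcome only:

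1. Define a visibility indicator: Medicaid or uninsured enrolment at the encounter if the warehouse holds it, otherwise any record there in the 12 months before the encounter.
2. Add a sensitivity analysis restricted to patients with the indicator.
3. Add the indicator to the balance check and propensity weights in section 5.5, Aim 1(c), noting that a prior-record flag corrects only part of the bias.
4. Report the indicator by group, time period and area.
5. Word the endpoint and conclusion as publicly funded treatment in Philadelphia.
6. State whether the 26% and 35% are all-payer or publicly funded rates and, if all-payer, give power at the observed visibility.

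The cost is one baseline variable from a file already being linked (with an extract starting 12 months earlier if prior records are used), one extra analysis and some rewording. The restricted set is smaller and, with prior records, under-represents people new to treatment, whom a linkage programme also aims to reach. It should support the main analysis, not replace it.

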#### **4.5. Data Management:**

Data that originates in the City of Philadelphia will stay within the jurisdiction of the City of Philadelphia. One person, acting as a shared Data Analyst between the Penn study team and the City of Philadelphia, will have access to City data. This individual will be funded using SPARROW grant dollars and have joint non-paid appointments in City departments providing de-identified data to the PIs for analysis. With the appointments in City departments, the individual will function as an intern within the City departments with access to department data. We will have a data sharing agreement that allows the provision of de-identified data to the PIs. Working as an intern in each data contributing department, the Data Analyst will be responsible for preparing the dataset, including data transformation of variables needed for the statistical model within the city setting. Only de-identified information will be sent from the City of Philadelphia to the PIs.

Interview data will be recorded and transcribed. Transcripts will only have a subject ID and not be specifically labeled by name. Interview data and photographs data will be managed by the PIs, [name] and [name]. Existing datasets will be transferred via a secure, electronic file transfer to computer server space dedicated to the proposed study and protected with firewall and encryption technologies managed by the IT Department of the University of Pennsylvania Perelman School Of Medicine. Drs. [name] and [name] will have master access to this drive and all data will only be accessible through a secured log-in. [name] is the project manager. [name] is the research coordinator. Other co-investigators, research coordinators, research assistants, and data analysts will only be granted access at the discretion of [name] and [name].

#### **4.6. Subject Follow-Up: N/A**

### **5. STUDY PROCEDURES:**

522 **5.1. Detailed Description:** Please see study design section for complete description of ARM  
523 and EMS opioid related care. The study is not involved in executing these city services,  
524 rather we are studying the outcomes using city administrative data.  
525

526 **5.2. Data Collection:** Please see study process section above. For interviews, we will find a  
527 convenient time for each individual interested in participating in the interview. Interviews  
528 will not take place during work hours unless approved by the individual's supervisor.  
529 Interviews will take place in a private location so that no one can hear the interview other  
530 than study staff. Interviews will be recorded and transcribed. Study staff will send each  
531 participant their own interview transcript, allowing the participant to review the transcript  
532 and provide comments or corrections. For photographs, the study team will get a list  
533 each morning of the locations of AR2 engagements over the prior 24 hours. Two  
534 members of the study team will then take a 360 photograph at the location of the  
535 engagement. Full, 360° sets of photographs will be taken from the street corner closest to  
536 each case (corresponding to the overdose location) and control location using a  
537 standardized field protocol. Photographs will be uploaded and stitched into 360° high-  
538 resolution panoramas using Microsoft Photosynth software. Trained coders blinded to  
539 case/control status will code all panorama photographs for 60 visible elements of the built  
540 and social environments using a detailed codebook. Photographs will be assessed by  
541 multiple coders and any discrepancies will be resolved by consensus. These photos will  
542 exclude people when at all possible. If people are inadvertently in the photograph, no  
543 effort will be made to identify them. The photos will be kept confidential and destroyed  
544 at the end of the study. No facial photographs will be published.  
545

546 **5.3. Genetic testing:** N/A  
547

548 **5.4. Use of deception:** This study does not include the use of deception.  
549

550 **5.5. Statistical Analysis:**  
551

552 **AIM 1 Analysis:**  
553

554 a. **Analysis plan and power calculation.** The unit of analysis is the patient-encounter.  
555 While our primary analysis will only include a patient's first encounter during the  
556 study period, we will consider analyses of patients with multiple encounters over the  
557 study period, possibly switching from comparison to intervention group, while taking  
558 care to avoid survivor bias. We will follow each patient from first encounter until  
559 either a subsequent overdose or death, whichever comes first. The following plan  
560 includes three designs - a paired encounter analysis, a comparison across time  
561 periods, and a difference-in-difference analysis. Our preferred approach to minimize  
562 the risk of confounding is the paired encounter analysis, but for some outcomes the  
563 anticipated number of paired encounters would provide insufficient power. We can  
564 address this limitation in statistical power by comparing outcomes across different

time periods when the AR2 is operating and when it is not, with a slightly greater risk of confounding, but likely to have greater power. A difference-in-difference analysis is our final fallback position.

- b. **Paired encounter analysis.** For the analysis of paired encounters (one AR2 and a non-AR2 occurring while the AR2 was on another call), we will use an exact McNemar's test for paired data for 0/1 outcomes (death, relapse) and a Cox proportional hazards model for paired data for censored time to event outcomes (time to treatment linkage, time to subsequent overdose). For each AR2 encounter we try to identify a non-AR2 encounter at the same time period within the AR2 response zone. If we find one, these pair of encounters are labeled as a pair and we will follow the patients for 60 days for linkage and non-fatal overdose, and 24 months for fatal overdose, and record outcomes. If multiple non-AR2 encounters happen simultaneously, then conditional logistic regression and stratified Cox models will extend the analysis from a 1-to-1 pairing to a 1-to-many matching. For our power calculations we assume a 1-to-1 pairing, a one-sided test for a reduction in adverse outcomes with  $\alpha = 0.05$  and a power level of at least 0.80. To detect a 50% reduction in the death rate attributable to the AR2 (assumed reduction from 10% to 5%), we need 370 pairs of encounters. To detect a 50% reduction in the rate of repeat non-fatal overdoses (from 30% to 15%), we need 105 pairs of encounters. To detect a 50% reduction in the hazard rate of time to subsequent overdose (equivalent to roughly 19% having a subsequent overdose within one year to 9.5%), we need 200 pairs of encounters. To detect an increase of 50% in the odds of seeking treatment within 60 days of an overdose (from 26% seeking drug treatment after an overdose within 60 days to 35% with AR2), we need 360 pairs of encounters.
- c. **Comparisons across time discontinuities.** For outcomes underpowered with a paired analysis, we will compare AR2 encounters during AR2 operational hours (10AM-6PM) to non-AR2 encounters outside of AR2's operational hours (6PM-10AM) within the Kensington zip code. Since comparison encounters will not be occurring at the same times as the AR2 encounters, there is a risk of confounding. We will first assess whether AR2 and non-AR2 patients encountered differ on likely confounders (e.g. age, race, sex, substance use profile such as type of drug, injected or not). Ideally focusing exclusively on patient encounters closest to AR2 time boundaries (near 10AM and 6PM) will provide sufficient observations and minimize the risk of confounding. If we find no differences (e.g. patients overdosing earlier in the day resemble those who overdose later in the day) then we will analyze the data as a simple binomial test of proportions (for 0/1 outcomes) or estimate the hazard ratio (for time to event outcomes). If we do find differences, then we will propensity score reweight comparison cases on age, sex, race, and substance use profile so that they do match. The following power calculation assumes no propensity score reweighting, but if propensity score reweighting is needed, the effective sample size, computed as  $(\sum w_i)^2 / \sum w_i^2$  where  $w_i$  is the propensity score weight, will need to equal the needed sample size in the power analysis. This depends on how many comparison encounters closely resemble the AR2 patients. To detect a 50% reduction in the death rate

attributable to the AR2 (assumed reduction from 10% to 5%), we need 380 encounters in each arm. To detect a 50% reduction in the rate of repeat overdoses (from 30% to 15%), we need 105 encounters in each arm. To detect a 50% reduction in the hazard rate of time to subsequent overdose (equivalent to roughly 19% having a subsequent overdose within one year to 9.5%), we need 200 encounters in each arm. To detect an increase of 50% in the odds of seeking treatment within 60 days of an overdose we need 380 encounters in each arm.

- d. **Difference-in-difference.** To further protect against confounding, we will compare encounters across times and places simultaneously. If within zip code 19134 those who overdose earlier in the day differ from those who overdose later in the day, but those differences are also reflected in the population outside zip code 19134, then a difference-in-difference analysis can use encounters outside 19134 to learn the expected difference between patients with early overdoses and later overdoses and appropriately adjust the within 19134 estimated treatment effect. For example, let  $\hat{p}_{01} - \hat{p}_{00}$  represent the estimated difference in the rate of seeking treatment for those outside 19134 during AR2 operating hours ( $\hat{p}_{01}$ ) and the rate of seeking treatment for those outside 19134 and outside of AR2 operating hours ( $\hat{p}_{00}$ ). Since the AR2 never operates outside of 19134 this difference captures the expected difference treatment seeking for those who overdose at different time periods. Then the difference-in-difference estimate  $((\hat{p}_{11} - \hat{p}_{10}) - (\hat{p}_{01} - \hat{p}_{00}))$  adjusts the treatment contrast within 19134 ( $\hat{p}_{11} - \hat{p}_{10}$ ) by subtracting off the observed difference by time of day for an untreated sample ( $\hat{p}_{01} - \hat{p}_{00}$ ). In practice, we compute ratios of odds ratios for 0/1 outcomes and ratios of hazard ratios for time-to-event outcomes.
- Because difference-in-difference estimates require estimation of three comparison quantities, the estimates are less precise and have greater sample size demands. We compute the number of encounters needed in each area (within 19134 and outside but near 19134) and time period (AR2 operational hours and AR2 non-operational hours). To detect a 50% reduction in the death rate attributable to the AR2 (assumed reduction from 10% to 5%), we need 600 encounters in each area in each time period. To detect a 50% reduction in the rate of repeat overdoses (from 30% to 15%), we need 170 encounters in each area and time period. To detect a 50% reduction in the hazard rate of time to subsequent overdose, we need 320 encounters in each area and time period. To detect an increase of 50% in the odds of seeking treatment within 60 days of an overdose we need 700 encounters in each area and time period.

